#### 2.8.2. Secondary Endpoints

Secondary endpoints include between-intervention differences in fasting TG, fasting plasma glucose, non–high-density lipoprotein cholesterol (non-HDL-C), apolipoprotein B (ApoB), and high-sensitivity C-reactive protein (hsCRP). Endothelial reactivity, assessed using the Endocheck^®^/Vicorder^®^ system, is also included among secondary outcomes. In addition, product acceptability will be evaluated at the end of each intervention period using a dedicated questionnaire based on 10-point rating scales assessing overall liking and key sensory attributes (e.g., taste, texture, and appearance). This assessment is intended to capture the tolerability and perceived palatability of the products, which are key determinants of adherence and feasibility in food-based interventions and help support the translational relevance of the study.

#### 2.8.3. Safety Endpoints

Safety endpoints will include the systematic collection and classification of adverse events (AEs), irrespective of their suspected relationship to the study products. Safety monitoring will be conducted throughout the study, and any clinically relevant changes in vital signs or laboratory parameters will be summarized descriptively by intervention period.

### 2.9. Assessments

#### 2.9.1. Laboratory Procedures

At Day −28 and at each subsequent visit, fasting blood samples will be collected to measure fasting plasma glucose, TG, total cholesterol, HDL-C, non-HDL-C, low-density lipoprotein cholesterol (LDL-C), very-low-density lipoprotein cholesterol (VLDL-C), apolipoprotein B100 (ApoB100), apolipoprotein AI (ApoAI), liver enzymes (aspartate aminotransferase (GOT), alanine aminotransferase (GPT), and gamma-glutamyl transferase (gamma-GT)), creatinine, and uric acid [10,11]. All assessments requiring fasting blood sampling will be scheduled in the morning following an overnight fast of at least 12 h; participants will be instructed not to consume any food or caloric beverages (including the study products) before the visit (water allowed). Whenever feasible, visits will be planned at a similar time of day across study periods to minimize diurnal variability. The TyG index will be calculated using the formula ln[fasting TG (mg/dL) × fasting glucose (mg/dL)/2] [9]. Samples will be processed according to standardized laboratory procedures: plasma will be separated by centrifugation shortly after collection, aliquoted into pre-labeled cryovials using coded identifiers to minimize freeze–thaw cycles, and stored in monitored −80 °C freezers with restricted access. Batched measurements will be prioritized when applicable to reduce inter-assay variability. Future ancillary analyses will be limited to cardiometabolic and inflammatory biomarkers consistent with the study objectives and will be conducted in accordance with ethics approval and applicable data protection regulations.

#### 2.9.2. Endothelial Function

Endothelial function will be assessed using the Endocheck^®^ system (BC Biomedical Laboratories Ltd., Vancouver, BC, Canada), integrated within the Vicorder^®^ device, under standardized testing conditions [12]. This cuff-based and largely automated approach provides a standardized assessment of brachial vasoreactivity during reactive hyperemia and has been reported to show acceptable repeatability and reproducibility in methodological evaluations. All assessments will be performed by the same trained operator to minimize inter-operator variability; the operator will undergo initial training and periodic retraining according to the manufacturer’s instructions and site standard operating procedures, consistent with our group’s extensive experience with this methodology in double-blind clinical trials [13,14]. The assessment will be performed during the same morning visit, in the fasting state and before any food intake. Participants will be instructed to remain in the supine position and to refrain from smoking and consuming caffeinated beverages for at least 12 h prior to the assessment [15]. Following a rest period, brachial pulse volume waveforms will be recorded at baseline and during reactive hyperemia induced by 5 min of cuff occlusion. As per the manufacturer’s instructions, one measurement will be obtained at each visit; repeat acquisition will be performed only if required due to inadequate signal quality or artifacts, and the single valid recording will be used for the analyses. Endothelial reactivity will be calculated as √(PV2/PV1), where PV1 and PV2 represent the pulse volume waveform area measured before and during hyperemia, respectively [16].

### 2.10. Adherence and Concomitant Therapies

Participants will be instructed to replace their usual carbohydrate staples with the assigned study products while maintaining an overall carbohydrate intake consistent with their habitual diet. Diet stabilization will be reinforced through scheduled nutritional visits and dietary counseling at each study visit (Table 3), during which any relevant intercurrent dietary changes will be actively reviewed and documented in the electronic case report form (eCRF). Concomitant medications and non-pharmacological products (including dietary supplements and homeopathic preparations) will be recorded in the eCRF. Chronic treatments will be permitted provided they have been stable for at least 3 months prior to enrolment and remain unchanged throughout the study. Adherence will be assessed at each visit using a standard food frequency questionnaire administered as part of the nutritional visit to capture overall dietary patterns and potential compensatory changes in staple carbohydrate intake, and further supported by the return of unused study foods and packaging.

### 2.11. Sample Size Determination

This is a pilot study exploring a comparison that has not been previously tested. The SD assumption (0.7 TyG units) was informed by large population datasets reporting a TyG SD of approximately 0.7 in adults. Assuming a two-sided alpha (α) level of 0.05, 80% power, and an estimated standard deviation (SD) of 0.7 units for the primary endpoint, the required sample size is estimated at 33 participants. With the planned enrolment target of 40 participants, the study will be able to detect a between-intervention difference of approximately 0.30–0.35 TyG units (within-participant, period-specific change), which we considered a clinically meaningful effect size for a proof-of-concept trial in this phenotype. To account for potential dropout (approximately 15%) and post hoc exclusions due to non-compliance, the target sample size will be increased to 40 participants. The study is not powered for secondary endpoints, which will be analyzed as exploratory outcomes and interpreted primarily using effect sizes and 95% confidence intervals to inform future trials.

### 2.12. Statistical Analysis Plan

Analyses will be performed using IBM SPSS Statistics (version 28.0). Continuous variables will be summarized as mean (SD) or median (interquartile range (IQR)), as appropriate, and categorical variables as counts and percentages. Treatment effects will be estimated within the crossover framework using linear mixed-effects models, including treatment, period, and sequence as fixed effects, and participant (nested within sequence) as a random effect to account for within-participant correlation. Accordingly, for the primary endpoint, the treatment effect will be interpreted as the between-intervention difference in period-specific change in TyG. Potential carryover effects will be explored by adding a treatment-by-period interaction term and by comparing period-specific baseline values; if evidence of carryover is observed, sensitivity analyses will be conducted, including analyses restricted to first-period data. Model assumptions (normality of residuals and homoscedasticity) will be assessed; when violated, data transformation and/or non-parametric sensitivity analyses (e.g., Wilcoxon signed-rank test for paired comparisons) will be considered, with paired estimates reported as supportive analyses. A per-protocol analysis will be performed excluding participants with major protocol deviations. Extreme values will be evaluated using the pre-specified approach, including Dixon’s Q test where applicable. All tests will be two-sided, with α = 0.05.

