## Abstract

Mild fasting hypertriglyceridemia is often accompanied by early insulin resistance and atherogenic dyslipidemia, making it an attractive target for pragmatic dietary prevention. This trial aims to determine whether substituting common cereal-based staples with functional low-glycemic index (low-GI) products improves the triglyceride–glucose (TyG) index in adults with fasting triglycerides >150 mg/dL. The GLOW study is an exploratory, randomized, double-blind, single-center crossover trial. Adults aged ≥18 years with fasting triglycerides >150 mg/dL and body mass index ≤30 kg/m^2^ will be enrolled. Participants will follow a stabilized Mediterranean-style diet and will complete two 28-day intervention periods in random sequence: (i) functional low-GI Altograno^®^ pasta, pizza base and flatbread; and (ii) conventional standard wholegrain products. Intervention periods will be separated by a 28-day washout. Study foods will be consumed as fixed daily substitutions of usual staple servings (one bread portion and one pasta or pizza portion). The primary endpoint is the between-intervention difference in TyG response over each period, defined as the period-specific change from the corresponding period baseline to the end-of-period assessment. The primary analysis will compare end-of-period TyG between interventions while adjusting for the period-specific baseline value. Secondary endpoints include fasting triglycerides and glucose, atherogenic lipoproteins (non–high-density lipoprotein cholesterol and apolipoprotein B), inflammation (high-sensitivity C-reactive protein), endothelial reactivity assessed with the Endocheck^®^/Vicorder^®^ system, and food acceptability. Safety endpoints include adverse event recording. Treatment effects will be estimated using linear mixed-effects models accounting for treatment, period and sequence, with prespecified carryover sensitivity analyses. A total of 40 participants will be recruited to generate feasibility data and effect size estimates. This protocol will provide crossover evidence on whether pragmatic, product-level low-GI staple substitution improves TyG and related cardiometabolic and vascular biomarkers in adults with suboptimal triglyceridemia, informing larger trials. Trial registration: ClinicalTrials.gov NCT07198789.

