### 2.3. Eligibility Criteria

Eligibility will be assessed at screening/baseline based on medical history, concomitant therapies, and laboratory findings. Inclusion and exclusion criteria are detailed in Table 1.

The BMI upper limit (≤30 Kg/m^2^) was selected to reduce metabolic heterogeneity and minimize confounding from obesity-related insulin resistance, inflammation, and endothelial dysfunction, thereby enabling a clearer evaluation of the effect of carbohydrate-quality substitution.

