### 2.6. Randomization, Allocation Concealment, and Blinding

Participants will be randomized in a 1:1 ratio to one of two intervention sequences using computer-generated randomization codes. Randomization codes will be retained in a sealed envelope and accessed only after database lock and completion of the primary data analysis. Study products will be pre-numbered, and dispensing will be documented in source records and in the case report forms.

The study will adopt a double-blind design, with both participants and investigators blinded to treatment allocation. Intervention and control products will be provided in identical packaging and labeled with a study code only. The treatment code will be disclosed only after database lock, unless unblinding is required for safety reasons. Emergency unblinding will be permitted only when deemed essential for clinical management or participant safety and welfare.

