#### 2.8.1. Primary Endpoint

The primary endpoint is the between-intervention difference in the TyG index response over each 28-day intervention period, defined as the within-participant, period-specific change from the corresponding period baseline (Day 0 for Period 1; Day 56 for Period 2) to the end-of-period assessment (Day 28 and Day 84, respectively). In the primary mixed-effects model, end-of-period TyG will be compared between interventions while adjusting for the corresponding period baseline value, yielding an estimate equivalent to a between-intervention difference in change. The crossover design will enable estimation of within-participant treatment effects while accounting for potential period-related influences.

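### The treatment-by-period carryover check cannot be estimated, because in this 2×2 crossover it duplicates the sequence term; the baseline check works only if made between sequences

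*Protocol article*

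**What the plan says.** The design is a two-sequence, two-period crossover. Section 2.6: "Participants will be randomized in a 1:1 ratio to one of two intervention sequences". Abstract: "Intervention periods will be separated by a 28-day washout".

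Section 2.12 specifies a linear mixed model "including treatment, period, and sequence as fixed effects, and participant (nested within sequence) as a random effect". Section 2.8.1 adds the period-specific baseline TyG as a covariate and defines the two baselines ("Day 0 for Period 1; Day 56 for Period 2").

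For carryover, section 2.12 names two checks: "Potential carryover effects will be explored by adding a treatment-by-period interaction term and by comparing period-specific baseline values". It then states the consequence: "if evidence of carryover is observed, sensitivity analyses will be conducted, including analyses restricted to first-period data".

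On selection, section 2.3 says: "Eligibility will be assessed at screening/baseline based on medical history, concomitant therapies, and laboratory findings". Table 3 marks eligibility assessment at both Day −28 and Day 0, and Table 1 requires fasting TG above 150 mg/dL.

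**The concern.** Two sequences in two periods give four cell means. An intercept plus treatment, period and sequence uses four parameters, so the fixed part of the model is already saturated. A fifth term built from treatment and period has nothing left to estimate.

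That leaves the baseline comparison as the only other named check, and the article does not say how it is made. If all participants' Day 0 values are set against their Day 56 values, the difference contains everything that changes over eight weeks in everyone, including the effect of dietary counselling at each visit (section 2.10, Table 3). Such a difference is not evidence of differential carryover.

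At stake is whether the trigger for the first-period sensitivity analysis means what it is taken to mean. The Discussion relies on this carryover evaluation to protect interpretability if such effects emerge.

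**Working it through.** The plan gives no figure for the carryover check, so there is none to reproduce. The inputs from the document are two sequences with 1:1 allocation (2.6), two periods (Abstract), the fixed effects (2.12), the baseline covariate (2.8.1), N = 40, SD 0.7 and a target difference of 0.30–0.35 TyG units (2.11).

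**1. Aliasing (no assumptions needed).** Code each factor −1/+1, where s is sequence, p is period and t is treatment:

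| Sequence (s) | Period (p) | Treatment (t) | t × p |
|---|---|---|---|
| −1 | −1 | −1 | +1 |
| −1 | +1 | +1 | +1 |
| +1 | −1 | +1 | −1 |
| +1 | +1 | −1 | −1 |

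In every row t × p = −s. Rank of the design matrix with 20 participants per sequence:

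- Intercept, t, p, s: 4 columns, rank 4. Adding t × p: 5 columns, rank 4.
- With the period-specific baseline covariate: rank 5 before and 5 after.
- Replacing s by t × p: 4 columns, rank 4. The model can be fitted, but the term is the sequence contrast relabelled.

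**2. What the sequence contrast can show.** It compares participants' two-period means between sequences. A carryover λ that affects Period 2 in one sequence shifts that contrast by λ/2. Assume SD 0.7 per measurement (the plan's figure, used here as a cross-sectional SD), within-participant correlation ρ of 0.3–0.8, 20 per sequence and no baseline covariate:

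SE = 0.7 × √((1+ρ)/2) × √(2/20)

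- ρ = 0.3: SE = 0.7 × 0.806 × 0.316 = 0.178
- ρ = 0.8: SE = 0.7 × 0.949 × 0.316 = 0.210

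Noncentral-t power on 38 df at two-sided 0.05:

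| λ | shift λ/2 | ρ = 0.3 | ρ = 0.8 |
|---|---|---|---|
| 0.30 | 0.150 | 13.0% | 10.7% |
| 0.35 | 0.175 | 15.9% | 12.8% |

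Baseline adjustment would change these values, so they are a guide to scale only.

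**3. Baseline check, pooled or between sequences.** Illustrative simulation with assumed between- and within-participant SDs of 0.5 and 0.3, N = 40:

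| Scenario | Pooled Day 0 vs Day 56 rejects | Day 56 − Day 0 change, between sequences, rejects |
|---|---|---|
| No carryover, no drift | 4.4% | 4.6% |
| No carryover, common drift −0.15 | 59% | 4.6% |
| Carryover −0.3 in one sequence | 54% | 58% |

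Hand check of the 59%: the SD of a paired difference is 0.3 × √2 = 0.424, its SE is 0.424/√40 = 0.067, and 0.15/0.067 = 2.24 standard errors. The pooled test responds about equally to harmless drift and to real carryover. The between-sequence test responds only to carryover.

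**4. Regression to the mean (assumed log-TG SDs 0.45 between and 0.25 within, population median 130 mg/dL).** If TG above 150 must hold at Day −28 and again at Day 0, the pooled mean change is −0.07 with 23% rejection, against 5.7% between sequences. If only Day −28 selects, the mean change is about 0 and pooled rejection is 5.6%.

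**The case against.** The strongest reply is that little is lost. The aliased contrast is the sequence effect, which the base model already estimates, so the first check is a redundant label and not a missing analysis. This is right about the information, but the sentence still describes an analysis that cannot be run, and a fuller analysis plan that repeated it would carry the same fault.

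On the second check, the article does not say that the comparison is pooled, and the full protocol may define it between sequences. That stands: the check is feasible and should not be called wrong.

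Four stronger readings are tempting, and the documents do not support them:

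- **That carryover cannot be examined at all.** A between-sequence baseline comparison is valid and available from data already planned.
- **That regression to the mean will trigger false carryover signals.** Section 2.3 and Table 3 place eligibility assessment at baseline as well as screening, but nothing says TG must exceed 150 mg/dL again at Day 0. Without that, the effect vanishes in step 4. Any false-flag rate also needs population values that the documents do not give.
- **That the plan switches its primary analysis after a carryover test.** Section 2.12 calls the first-period analysis a sensitivity analysis, and nothing replaces the primary estimate. Lower precision there is expected and is not an error.
- **That carryover is named as the main threat.** The Discussion lists it as one limitation among several.

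**Conclusion.** The point holds in two parts. First, the treatment-by-period check has zero degrees of freedom in this design. This is exact, needs no assumptions and does not depend on sample size. Second, the baseline check is feasible but informative about carryover only when made between randomized sequences, and the article leaves this open. The size of the problem under a pooled reading depends on assumed SDs and drift, so the figures in steps 3 and 4 show a mechanism and do not predict rates for this trial.

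Severity is minor to moderate. The primary estimate comes from the model without the added term and is unaffected, carryover is exploratory, and a signal leads only to sensitivity analyses.

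**What to change.** In section 2.12:

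1. Delete the treatment-by-period term.
2. Report the existing sequence contrast with its 95% confidence interval. State that it is a low-power between-participant contrast and cannot separate carryover from a sequence difference or a treatment-by-period interaction.
3. Define the baseline check as a between-sequence comparison of Day 56 TyG adjusted for Day 0 TyG, and note that it shows only carryover still present at Day 56.
4. Optionally, report the baseline-adjusted Period 1 estimate as supportive whatever the carryover result. This is a preference, not the correction of an error.

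The cost is a few sentences, with no new data, visits or participants. The wording should be settled before database lock and unblinding.

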Nevertheless, several limitations should be considered. As a single-center pilot trial, findings will primarily inform feasibility, directionality, and effect-size estimation rather than definitive clinical efficacy. Each intervention period lasts 28 days and the protocol relies on surrogate metabolic and vascular biomarkers rather than hard clinical outcomes; accordingly, any observed improvements should be interpreted as short-term biomarker modulation and proof-of-concept evidence, not as durable cardiometabolic risk reduction. Carryover and period effects remain intrinsic to crossover designs, and the planned evaluation of carryover signals and sensitivity analyses restricted to first-period data will be important for preserving interpretability if such effects emerge. Blinding may be challenged by sensory differences between products, and residual variability in background diet may persist despite counseling and stabilization measures. Endothelial reactivity will be assessed using the Endocheck^®^/Vicorder^®^ system; while practical and standardizable for a double-blind intervention setting, this approach is less extensively validated than ultrasound-based FMD and does not have a well-established minimal clinically important difference; therefore, vascular findings will be interpreted primarily using effect sizes and confidence intervals. Moreover, eligibility is restricted to adults with BMI ≤ 30 Kg/m^2^; thus, generalizability to individuals with obesity or more advanced metabolic impairment may be limited. Because the functional and control products differ in fiber, protein, and labeled carbohydrate content, any observed effects will reflect the combined influence of the overall nutritional matrix and carbohydrate quality, and cannot be attributed to glycemic index alone.

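### The first-period analysis is run only after a carryover signal, so when it appears its false-positive rate is about 15–25% rather than 5%

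*Protocol article*

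**What the plan says.** Section 2.6 describes the design: "Participants will be randomized in a 1:1 ratio to one of two intervention sequences". The model in section 2.12 is one of "linear mixed-effects models, including treatment, period, and sequence as fixed effects, and participant (nested within sequence) as a random effect", and section 2.8.1 adds that "end-of-period TyG will be compared between interventions while adjusting for the corresponding period baseline value".

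Section 2.12 names two carryover checks: "Potential carryover effects will be explored by adding a treatment-by-period interaction term and by comparing period-specific baseline values". What follows depends on the result: "if evidence of carryover is observed, sensitivity analyses will be conducted, including analyses restricted to first-period data". No threshold for such evidence is given, but the section closes with a general rule: "All tests will be two-sided, with α = 0.05". The limitations paragraph of the Discussion gives the conditional analysis weight, saying that "sensitivity analyses restricted to first-period data will be important for preserving interpretability if such effects emerge".

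**The concern.** A first-period comparison that is prespecified and always reported is an ordinary parallel-group test with a 5% error rate. Here it is reported only when another test on overlapping data looks unusual. If sequence A happens by chance to contain people with higher Day 28 values than sequence B, that one imbalance produces both an apparent carryover signal and an apparent first-period treatment difference. The reader would then see the first-period result mainly in the trials where it is least trustworthy, with the Discussion's assurance that it protects interpretation.

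The trial is a pilot intended to supply an effect-size estimate for later studies. An estimate shown only after selection on the same imbalance tends to be exaggerated, and that matters here as much as the p-value does.

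**Working it through.** **Inputs from the protocol article.** Two sequences, 1:1 (2.6); 40 enrolled (2.11), so 20 per sequence; two-sided 0.05 (2.12); baseline adjustment (2.8.1); visits at Days 0, 28, 56 and 84.

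**Assumed, because the article does not give them.** A 0.05 trigger, taken from the general alpha; within-person correlation ρ of 0.5–0.8 between visits; no treatment effect and no carryover. The rates do not depend on the SD.

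**The plan's own figure.** The only error rate stated is 0.05. Run unconditionally, the first-period test reproduces it: 4.9–5.2% in every simulated scenario.

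**Step 1: the interaction is the sequence effect.** Code treatment (functional +1, control −1) and period (first +1, second −1). The product is:

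| Sequence | Period 1 | Period 2 |
|---|---|---|
| Functional then control | (+1)(+1) = +1 | (−1)(−1) = +1 |
| Control then functional | (−1)(+1) = −1 | (+1)(−1) = −1 |

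That column is sequence, which is already in the model. The carryover test is therefore the between-sequence test on data from both periods, including period 1.

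**Step 2: how strongly trigger and test are linked.** Take unit variance, equal correlation ρ and baseline coefficient ρ, as a large-sample approximation. Let R1 = Y28 − ρY0 and R2 = Y84 − ρY56.

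- Var(R1) = Var(R2) = 1 − ρ² and Cov(R1, R2) = ρ(1 − ρ)², so corr(R1, R2) = c = ρ(1 − ρ)/(1 + ρ).
- Baseline-adjusted interaction trigger against first-period test: corr(R1 + R2, R1) = √((1 + c)/2). At ρ = 0.5, c = 0.167 and the correlation is 0.764. At ρ = 0.8, c = 0.089 and it is 0.738.
- Day 56 comparison adjusted for Day 0, against first-period test: ρ/(1 + ρ) = 0.333 at ρ = 0.5 and 0.444 at ρ = 0.8.
- Day 56 comparison unadjusted: ρ(1 − ρ)/√(1 − ρ²) = 0.289 and 0.267.

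For two standard normal statistics with these correlations, P(|Z1| > 1.96 given |Z2| > 1.96) is about 40% and 37% for the interaction trigger, 11% and 16% for the adjusted Day 56 trigger, and 9% for the unadjusted one. With zero correlation it would be 5%.

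**Step 3: simulation with 20 per sequence.** False-positive rate of the baseline-adjusted first-period test at 0.05, counted only in trials where the trigger fired:

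| Trigger at 0.05 | Fires in | First-period test falsely significant |
|---|---|---|
| None (always run) | – | 5% |
| Day 56 baseline comparison alone | about 5% | about 8–16% |
| Baseline-adjusted interaction alone | about 5% | about 35–39% |
| Either signal, interaction tested on unadjusted totals, Day 56 adjusted for Day 0 | about 10% | about 15–19% |
| Either signal, baseline-adjusted interaction | about 10% | about 22–25% |

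The single-trigger rows agree with Step 2. With autoregressive correlation of 0.7–0.8 the last row stays at 23–25%. Loosening the interaction trigger to 0.10 lowers its own row to 25–29%.

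**Step 4: share of all null trials.** 0.10 × 0.15 = 1.5% to 0.10 × 0.25 = 2.5% would show a triggered and spurious first-period result.

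**The case against.** The strongest reply is that nothing confirmatory hangs on this step. The article calls it a sensitivity analysis within an exploratory pilot, and no sentence lets it replace the two-period model. That stands. A reader might infer the classic two-stage procedure, in which the first-period result becomes the conclusion and the trial's overall error rate is inflated; the documents do not support that.

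Two other strong readings also fail.

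- A reader might infer that most triggered first-period results would be false. That needs an unadjusted Day 28 test, whereas section 2.8.1 fixes baseline adjustment for the primary comparison and nothing suggests dropping it here.
- A reader might infer that a quiet carryover check tells us nothing. Section 2.11 gives the planning inputs: "Assuming a two-sided alpha (α) level of 0.05, 80% power, and an estimated standard deviation (SD) of 0.7 units for the primary endpoint". If 0.7 is read as the single-visit SD, which is an assumption, a Day 56 comparison adjusted for Day 0 has about 42–72% power for a carryover of 0.35 still present at Day 56. The adjusted first-period estimate has about the same power for a treatment effect of 0.35. That is limited, but not nothing.

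It is also fair that the trigger seldom fires under the null, that the Day 56 check alone inflates much less than the interaction, and that the threshold for evidence may be set in a fuller document. The missing threshold is not the complaint. The conditional rule is stated in the article, and its inflation persists at either 0.05 or 0.10. Calling the result a sensitivity analysis does not undo the selection that decides when it is seen.

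**Conclusion.** The point holds as a defect in a supportive analysis. As written, the first-period test appears in about 10% of trials with no effect and no carryover, and in those it is falsely significant in about 15–25%, three to five times nominal. The interaction signal drives most of this (about 35–39% alone); the Day 56 baseline signal contributes less (about 8–16% alone). These figures rest on 20 per sequence, a 0.05 trigger, baseline adjustment and the assumed correlation of 0.5–0.8. The primary two-period analysis is unaffected. The rule should be changed because it is prespecified, the Discussion leans on it, and it is cheap to repair.

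**What to change.** Replace the conditional sentence in section 2.12 with wording such as:

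> The two-period mixed model remains the primary analysis whatever the carryover assessment shows. The baseline-adjusted first-period estimate with its 95% CI will be reported in all cases as supportive. The carryover (sequence) contrast and the between-sequence comparison of Day 56 baselines will be presented as estimates with 95% CIs and will not determine which analyses are reported.

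Remove the separate treatment-by-period term, since sequence already carries it. Amend the Discussion sentence so that it no longer presents the first-period analysis as a safeguard called on when carryover emerges.

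The cost is wording and one estimate that is always reported. The downside is that a wide first-period interval is shown even when nobody suspects carryover.
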